### Control

Individuals in the control group will continue with their normal activities. Should they decide to join a singing group outside the research they will not be excluded but data will be collected on these activities.

### Sample size

A power calculation was carried out for the primary outcome (health related quality of life measured on the York version of the SF-12). There are no previous randomised controlled trials evaluating the impact of singing groups on quality of life in this population. Using data from quasi-experimental and observational studies we hypothesise that a minimally important difference in health related quality of life between the intervention group and control groups is in the order of 5 points on the York SF-12, equivalent to a medium effect size difference of 0.5. To detect this difference using a two-tailed test, alpha of 0.05 and power at 80% requires 63 participants in each of the two arms, a total of 126. We anticipate 5 singing groups and 5 controls and need to take account of any clustering effect in calculating sample size. We have used a conservative estimate of intra-class correlation coefficient of 0.02, similar to general practice populations and a cluster size of 12. This inflates the required sample size by a factor of 1.2, 77 in each group, a total of 154. Previous research would suggest the loss to follow up at 6 months for this population would be in the order of 20% and this further inflates the sample size to 92 in each group, a total of 184. We do not anticipate that all those enquiring would be willing to take part in the evaluation but we do have evidence that the consent rate would be in the order of 70%. This would mean we would require a total of 240 potential participants, 24 in each singing group and control group over the course of the study.

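### Sample size: a cluster size of 12 does not fit five groups per arm, so the 1.22 design effect and the 77 per arm do not describe the planned design

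*Protocol article*

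**What the plan says.** All the figures stand in the Sample size section of the protocol article.

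- Target difference: "in the order of 5 points on the York SF-12, equivalent to a medium effect size difference of 0.5".
- Size before clustering: "two-tailed test, alpha of 0.05 and power at 80% requires 63 participants in each of the two arms, a total of 126".
- Number of groups: "We anticipate 5 singing groups and 5 controls and need to take account of any clustering effect in calculating sample size".
- Clustering inputs: a "conservative estimate of intra-class correlation coefficient of 0.02, similar to general practice populations and a cluster size of 12".
- Result: "This inflates the required sample size by a factor of 1.2, 77 in each group, a total of 154".

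Other sections agree on five. Recruitment speaks of five venues, Randomisation and consent allocates individuals within five areas, and Intervention has all clubs run the same programme at the same time. No section gives more than five groups per arm.

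**The concern.** The number of groups, the group size and the number per arm are tied together: any two fix the third. The section states all three, and they disagree. The design effect is computed for groups of 12, but five groups can reach 77 per arm only if they are larger.

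With the number of groups fixed, each added participant raises the group size and hence the design effect. The inflation and the sample size therefore have to be solved together. Taking the group size as a free input of 12 makes the inflation too small for the design under the section's own method. The Discussion presents the power calculation as one of the trial's advances over earlier studies, so it should describe the trial that will be run.

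**Working it through.** **Inputs** (all from Sample size): standardised difference 0.5; two-sided alpha 0.05; power 80%; ICC 0.02; cluster size m = 12; five groups per arm. Power uses the normal approximation, with DE for the design effect.

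**1. Reproduce the plan's figures.**
- Unclustered: n = 2 × (1.96 + 0.84)² / 0.5² = 62.8, so 63 per arm. This agrees.
- DE = 1 + (m − 1) × ICC = 1 + 11 × 0.02 = 1.22.
- 63 × 1.22 = 76.9, so 77 per arm. This agrees. The printed factor of 1.2 is 1.22 rounded, since 63 × 1.2 would be 75.6.

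**2. Test the cluster size against the design.**
- 5 × 12 = 60 per arm, below both 63 and 77.
- 77 / 12 = 6.4 groups per arm would be needed, against five planned.
- 77 / 5 = 15.4 analysed per group.
- Loss to follow-up does not bring this down to 12. The stated 92 per arm less 20% is 73.6, and 73.6 / 5 = 14.7 per group.

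**3. Power at the stated 77, five groups, both arms inflated.**
- DE = 1 + (15.4 − 1) × 0.02 = 1.288.
- Power = Φ(0.5 × √(77 / (2 × 1.288)) − 1.96) = Φ(0.77) = 78%.
- For comparison, DE 1.22 at 77 gives Φ(0.5 × √(77 / 2.44) − 1.96) = Φ(0.85) = 80%.

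**4. Self-consistent size, five groups, both arms inflated.** Put m = n / 5 into the inflation:
- n = 63 × [1 + (n/5 − 1) × 0.02] = 61.74 + 0.252 n.
- n = 61.74 / 0.748 = 82.5, so 83 analysed per arm (166 in all).
- m = 82.5 / 5 = 16.5 and DE = 1.31.
- Against the plan: 83 − 77 = 6 more analysed per arm, about 8%.

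**5. Alternative: clustering in the singing arm only.** The variance of the difference is then proportional to (DE + 1) / n instead of 2 DE / n:
- n = 31.5 × (DE + 1) = 31.5 × (1.98 + 0.004 n) = 62.37 + 0.126 n.
- n = 62.37 / 0.874 = 71.4, so 72 analysed per arm.
- At 77: Φ(0.5 × √(77 / 2.288) − 1.96) = Φ(0.94) = 83%.

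**The case against.** **Controls may not be clustered.** This is the strongest objection. Individuals are randomised within areas, so area differences are common to both arms. The Control section has controls carry on with their normal activities, so no control group meets. Effectiveness analysis describes the clustering as arising from the singing groups. With clustering in that arm only, step 5 shows that 77 is more than enough, because inflating both arms outweighs the low cluster size. This stands as a limit on the consequence: a reader might infer that the trial is underpowered, and the documents do not establish that. It does not rescue the paragraph, which counts five control groups, inflates both arms and makes no one-arm argument.

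**Baseline adjustment.** The planned analysis of covariance would also recover power. As an approximation, multiply the variance by 1 − r², where r is the correlation between baseline and six months. Step 3 then reaches 80% when 1 − r² = 77 / (62.8 × 1.288) = 0.952, that is, r of about 0.22. The document gives no value for r and the calculation takes no credit for it.

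**Two waves of 12.** The section's last sentence mentions 24 potential participants per group over the study, which might suggest two waves. But those 24 are counted before consent, and the clubs run concurrently.

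**Stronger readings that do not hold.**
- One might use the randomised group size, 92 / 5 = 18.4. The design effect of the analysis depends on those analysed, so that figure does not belong with 77.
- One might carry 83 through 20% loss to 83 / 0.8 = 104 per arm and set it against the stated 92. That mixes in a separate matter: 77 / 0.8 is already 97, so 5 of the 12 extra per arm come from the loss step.
- One might call the ICC of 0.02 too low. The section gives a basis for it, and nothing in the document supports a larger value.

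**Conclusion.** The point holds as an internal contradiction: five groups, 12 per group and 77 per arm cannot all be true. Under the plan's stated method the clustering inflation should be about 1.31 instead of 1.22 at the self-consistent size, which means 83 analysed per arm instead of 77. If 77 is kept, power is about 78% instead of 80%.

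These figures assume ICC 0.02, equal group sizes, both arms clustered, the normal approximation and no gain from baseline adjustment. They leave loss to follow-up aside. The size is modest, and its direction depends on the treatment of the control arm: if only the singing arm is clustered there is no shortfall. What is wrong is the stated calculation. The documents do not show that the planned number is inadequate.

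**What to change.** Reword the clustering sentences in Sample size so that the number of groups, the group size and the number per arm agree. Either of these would do:

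- Keep both arms clustered. Take the cluster size as the analysed number per arm divided by five, and state either the required size (83 analysed per arm) or the power at 77 (about 78%).
- State that only the singing arm is treated as clustered, because controls continue their normal activities. Then give about 72 analysed per arm as the requirement, or about 83% power at 77, at ICC 0.02.

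The cost is one reworded paragraph. Randomisation, data collection and analysis do not change. Under the first option, keeping 77 means reporting slightly lower power, and keeping 80% power means 6 more analysed participants per arm, before any allowance for loss.

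### The allowances for 20% loss and 70% consent are too small: 184 randomised and 240 approached do not deliver the 154 analysable participants the plan requires

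*Protocol article*

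**What the plan says.** The Sample size section of the protocol article builds its target in four steps.

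1. **Base size.** The target difference is "5 points on the York SF-12, equivalent to a medium effect size difference of 0.5". The section states that a "two-tailed test, alpha of 0.05 and power at 80% requires 63 participants in each of the two arms, a total of 126".
2. **Clustering.** It assumes an "intra-class correlation coefficient of 0.02, similar to general practice populations and a cluster size of 12", and concludes: "This inflates the required sample size by a factor of 1.2, 77 in each group, a total of 154".
3. **Loss to follow-up.** Expected loss at six months is put at about "20% and this further inflates the sample size to 92 in each group, a total of 184".
4. **Consent.** About 70% of enquirers are expected to consent. The section then says "This would mean we would require a total of 240 potential participants", which it spreads as 24 to each singing and control group.

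The section names no formula for steps 3 and 4. The Randomisation and consent section makes the order clear: only people who have returned a questionnaire with consent are randomised. So 184 is the number randomised, and 240 is the pool before consent.

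**The concern.** An allowance for attrition must make the number left after attrition equal the number required. If a fraction *L* is lost, the requirement is divided by (1 − *L*); multiplying by (1 + *L*) always gives too few. The same holds for consent: if a fraction *c* consents, the number to randomise is divided by *c*.

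The printed 92, 184 and 240 look like products of 1.2 and 1.3. If so, the plan falls short of its own requirement at both steps, and the 80% power it claims does not belong to the sizes it prints. A team that treated 240 enquirers as enough would also miss the plan's own randomisation target. The article presents its power calculation as one of its advances over earlier studies, so the calculation should be internally consistent.

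**Working it through.** **Inputs, all from the Sample size section:** two-sided alpha 0.05; power 80%; standardised difference 0.5; equal arms; intra-class correlation 0.02; cluster size 12; loss 20%; consent 70%.

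**Steps that are sound**

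- Base size, normal approximation: n = 2 × (1.96 + 0.8416)² / 0.5² = 62.8, so 63 per arm (126). This matches the plan.
- Design effect: 1 + (12 − 1) × 0.02 = 1.22, and 63 × 1.22 = 76.9, so 77 per arm (154). This matches the plan; its printed factor of 1.2 is 1.22 rounded.

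**Reproducing the plan's next two figures**

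| Step | Multiplying | Dividing | Printed |
|---|---|---|---|
| Loss, per arm | 77 × 1.2 = 92.4 | 77 / 0.8 = 96.25 | 92 |
| Loss, total | 154 × 1.2 = 184.8 | 154 / 0.8 = 192.5 | 184 |
| Consent | 184 × 1.3 = 239.2 | 184 / 0.7 = 262.9 | 240 |

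Starting from the plan's own 77 and 154, only multiplication reproduces the printed numbers. The multipliers are inferred, but the shortfalls below do not depend on that inference.

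**What the printed numbers deliver at the plan's own rates**

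- 184 × 0.8 = 147.2 analysable (73.6 per arm), against 154 required: about 7 short.
- 240 × 0.7 = 168 randomised, against 184 stated: 16 short.
- 168 × 0.8 = 134.4 analysable (67.2 per arm), against 154: about 20 short.

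**Power**, with effective size per arm m = n / 1.22 and power = Φ(0.5 × √(m/2) − 1.96):

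| Analysed, total | Per arm | Effective per arm | Power |
|---|---|---|---|
| 154 | 77 | 63.1 | 80.2% |
| 147.2 | 73.6 | 60.3 | 78.4% |
| 134.4 | 67.2 | 55.1 | 74.7% |

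**Corrected chain**

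- Loss: 77 / 0.8 = 96.25, so 97 per arm and 194 in total (193 if the division is done on 154).
- Consent: 194 / 0.7 = 277.1, so 278. Other rounding orders give 275 (154 / 0.8 / 0.7, unrounded) or 276 (193 / 0.7).
- Check: 278 × 0.7 = 194.6 randomised, and 194 × 0.8 = 155.2 analysable, which meets 154.

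**The per-group figure.** 24 is 240 / 10, so it counts people who will not consent and will never be in a group. With 184 randomised, the average is 18.4 per group.

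**The case against.** The arithmetic itself is hard to dispute. The case on the other side is about how much it matters.

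- **The loss step is small.** It costs under 2 points of power, and both rates are given only as approximate. The printed 92 would be exact for a loss of 1 − 77/92 = 16.3%. This stands as a comment on size, but the plan states 20%. For consent, 184/240 is 76.7%, not the stated 70%.
- **Baseline adjustment is not credited.** The Effectiveness analysis section plans analysis of covariance on the SF-12. Dividing the effective size by (1 − r²), where r is the baseline to six-month correlation, 147 analysed reaches about 80% power at r = 0.2 and 89% at r = 0.5; 134 analysed reaches about 80% at r = 0.35. The article gives no value of r, so these are assumptions. They suggest the trial could well have adequate power, but they do not make the printed derivation right.
- **Clustering may affect one arm only.** Controls simply continue their usual activities. With the design effect of 1.22 applied only to the singing arm, 147 analysed gives about 82% power and 134 about 79%. The plan, however, inflates both arms, and its claim must be judged on that basis.
- **240 is not a cap.** Nothing says that recruitment ends at 240 enquiries, and the number to randomise is stated separately as 184. This stands: the 75% figure is conditional. The contradiction between 240 at 70% consent and 184 randomised does not depend on any stopping rule.

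**Conclusion.** The concern holds. At the plan's own rates, 184 randomised gives about 147 analysable participants instead of 154, and 240 approached gives 168 randomised instead of 184. Nothing elsewhere in the article corrects either figure.

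On the plan's stated basis, power is about 78% if 184 are randomised. It is about 75% if recruitment stops at 240 enquirers. The consent step does more harm than the loss step.

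These figures assume a standardised difference of 0.5, a design effect of 1.22 in both arms, exactly 20% loss and 70% consent, a normal approximation, and no gain from baseline adjustment. Such a gain could offset the loss of power in practice, but the sample size section does not claim it. The design and the planned analysis are unaffected; what is wrong is the stated sample size and the power attached to it.

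**What to change.** Rewrite the end of the Sample size paragraph in one of two ways.

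1. **Correct the numbers.** Replace 92 per arm and 184 in total with 97 and 194, and replace 240 with 278. This needs 10 more participants randomised and 38 more enquirers.
2. **Keep the numbers and restate what they deliver.** 184 randomised gives about 147 analysed and about 78% power. 240 enquirers gives 168 randomised, about 134 analysed and about 75% power. This costs only the rewording. If credit is to be taken for baseline adjustment, state the assumed correlation and show the calculation.

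In either case, make the number randomised the recruitment target and treat the enquirer figure as a forecast. Replace 24 per group with a figure for people randomised: about 18 per group for 184, or about 19 for 194.

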### Outcomes

The study will use standardised instruments with demonstrated validity, reliability and responsiveness. In addition, data will be collected on health and social care service utilisation and activities (including musical and singing activities) engaged in over a period six months prior, and six months after randomisation. Outcomes will be measured using a postal questionnaire.

#### Primary outcome

The primary outcome measure will be self-assessed health related quality of life assessed using the York SF-12 [23]. This is a frequently used measure that has been validated for use with older people and for which population norms exist. The twelve multiple choice questions cover both physical and mental domains of health. Most questions ask about health over the past week. Measures will be taken at baseline (prior to randomisation), 3 and 6 months after randomisation. The instrument allows the generation of an overall health-related quality of life score and additional two component scores addressing physical and mental health aspects of health-related quality of life.

#### Secondary outcomes

Health utility will be measured using the EQ-5D [24]. This is a short, 3-level, 5-dimensional instrument allows the generation of Quality Adjusted Life Years. It is routinely used in the economic evaluation of health care and recommended for cost-effectiveness analyses.

Anxiety and depression will be measured using the Hospital Anxiety and Depression Scale (HADS) [25]. This has validity for use in community as well as hospital settings and has been used in previous studies evaluating arts and music interventions.

Health and social care service utilisation will be measured using a specially designed questionnaire used in a number of evaluations involving older populations.

All secondary outcomes will be measured at baseline, and then 3 and 6 months after randomisation.

In addition we will collect process data consisting of individual attendance at singing groups for participants and information on who delivered singing group sessions.

### Data analysis

#### Effectiveness analysis

Data analysis will be conducted blind to the allocation of participants. The primary analysis will be intention to treat, where participants are analysed as part of their randomised group irrespective of their attendance. This provides the most pragmatic estimate of effectiveness. The primary outcome measure, the SF-12, will be analysed at 6 months using analysis of covariance to adjust for baseline differences between the groups. Due to the clustered nature of the study in which participants are nested within singing groups multi-level modelling will be undertaken to adjust for any cluster effects. Results will be presented as means and 95% confidence intervals. Secondary outcomes will be analysed in a similar manner. We will also explore the potential efficacy of the intervention by conducting a per protocol analysis in which only those participants who attended at least 50% of sessions are included. Other secondary analysis will include a regression analysis to explore both potential predictors of outcome and any baseline x treatment interactions.

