#### Randomisation and consent

All individuals indicating an interest in taking part will be sent a baseline questionnaire. They will also be sent an information sheet outlining the purpose of the study and what to expect if taking part, plus a consent form to be returned with the questionnaire.

All returned, consented questionnaires will be randomly assigned to either intervention or control arm within one of five geographical areas. Randomisation will be conducted using the secure remote randomisation service based at the University of Kent. Because of the known preponderance of women in singing groups, stratification by gender will be used. Individuals who would attend together if allocated to a singing group (e.g. couples or friends providing transport) will be randomised in pairs on request.

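### Allocation is stratified by area and gender, but the primary model as described names neither; if its clusters are the ten area-by-arm groups, between-area variation is charged to the treatment comparison

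*Protocol article*

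**What the plan says.** **Allocation** (Randomisation and consent). Consenting individuals are "randomly assigned to either intervention or control arm within one of five geographical areas", and "stratification by gender will be used" because women predominate in singing groups. The Recruitment section also tells volunteers that allocation happens inside their chosen locality. Area and gender are therefore both design factors.

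**Analysis** (Effectiveness analysis). The SF-12 "will be analysed at 6 months using analysis of covariance to adjust for baseline differences between the groups". The next sentence adds that because "participants are nested within singing groups multi-level modelling will be undertaken to adjust for any cluster effects". Secondary outcomes are to be handled similarly. Neither area nor gender is named. The cluster named is the singing group, and no unit is given for controls, who carry on with their usual activities and do not meet.

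**Clusters** (Sample size). "We anticipate 5 singing groups and 5 controls and need to take account of any clustering effect in calculating sample size". This is the only place where the number of clusters is given. It counts control groups as units alongside the singing groups, which makes one cluster per arm in each area.

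**The concern.** Randomising within area means that a high-scoring or low-scoring area shifts both arms equally and drops out of the difference between them. The analysis benefits only if the model knows which singing group and which control group share an area. A statistician who takes the ten groups of the sample-size section into the multi-level model of the analysis section, with no area term, treats them as ten unrelated clusters. The model then reads differences between areas as noise in the treatment effect.

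The estimate stays unbiased, but its standard error is too large, and the trial gives up precision that its own stratification provided. Chance imbalance by area or gender among those with 6-month data would also go unadjusted. The sample-size section expects about 20% loss, and men are likely to be few.

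**Working it through.** **Inputs from the Sample size section.** A difference "in the order of 5 points on the York SF-12, equivalent to a medium effect size difference of 0.5", so SD = 5/0.5 = 10; two-sided alpha 0.05 and 80% power; "a conservative estimate of intra-class correlation coefficient of 0.02"; cluster size 12; ten groups.

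**Assumed.** The share of outcome variance lying between areas (rA). The documents give none; 2%, 5% and 10% are used, with near-zero values as a check.

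**Step 1: the plan's own figures.** n per arm = 2(1.96 + 0.84)²/0.5² = 62.7, so 63. Design effect = 1 + (12 − 1) × 0.02 = 1.22, and 63 × 1.22 = 76.9, so 77 per arm. Both reproduce.

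**Step 2: standard error of the arm difference.** Take 77 analysed per arm over five areas, total variance 100, area variance vA = 100·rA, remainder vE = 100 − vA, and for this step no separate singing-group variance.

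- Area in the model: √(2vE/77)
- Ten unmatched cluster intercepts, no area: √(2(vA/5 + vE/77))
- Plain ANCOVA, no area or cluster term: √(2(vA + vE)/77)

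Worked at rA = 2%: √(2 × 98/77) = 1.60; √(2(0.4 + 1.273)) = 1.83; √(200/77) = 1.61.

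| rA | Area in model | Ten clusters, no area | Plain ANCOVA |
|---|---|---|---|
| 2% | 1.60 | 1.83 (15% larger) | 1.61 (1% larger) |
| 5% | 1.57 | 2.11 (35% larger) | 1.61 (3% larger) |
| 10% | 1.53 | 2.52 (65% larger) | 1.61 (5% larger) |

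A random intercept for area, instead of fixed effects, gives the same standard error as the first column.

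**Step 3: power and type I error by simulation.** 200,000 trials, five areas, 15 analysed per area and arm, effect 0.5 SD, singing-group ICC 0.02 in the singing arm, Wald z tests. Repeat runs agreed to within about 0.5 percentage points.

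| rA | Ten clusters: power / type I | Area fixed + group random: power / type I |
|---|---|---|
| 2% | 73% / 3.7% | 77% / about 5% |
| 5% | 65% / 2.6% | 78% / about 5% |

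With very little area variance the advantage goes: at 0.5% power is 77.3% against 77.0%, and at zero 78.5% against 76.6%, slightly worse with area.

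**Step 4: the same simulations with t tests on cluster-level degrees of freedom.** Ten clusters less two arm means leaves 8. Fitting area costs four more and leaves 4. Power for ten clusters against area-adjusted is about 0.60 against 0.49 at rA = 2%, and about 0.51 for both at 5%.

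No separate calculation was made for gender. Under plain ANCOVA, strata explaining a share R² of the residual variance widen the interval by 1/√(1 − R²): 2.6% at R² = 0.05 and 5.4% at 0.10.

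**The case against.** The strongest reply is that this is a condensed article, and a full covariate list is normally left to an analysis plan that is not shown. The analysis section is silent on area and gender and does not exclude them. A reader might infer that the model adjusts for baseline and nothing else. The text does not support that: it never says baseline is the sole adjustment, and the following sentence adds a cluster term.

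The costly model is also one reading among several. The ten groups appear in the sample-size arithmetic, not in the analysis section. There is one singing group per area, so if the level is coded by area, the area variation is already removed. The area variance is assumed, and baseline SF-12 adjustment may absorb much of any stable difference among five areas that all lie in East Kent.

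A reader might also infer that power is lost for nothing and that the repair is free. Step 4 shows otherwise: with small-sample degrees of freedom, adding area can lower power. Any error runs in the conservative direction.

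These replies limit the size and the certainty. They do not remove the mismatch. The article does describe its primary model, names a cluster that is not the randomisation stratum, counts clusters in a way that invites the unmatched model, and gives controls no unit. An analysis plan written faithfully from these sections could go wrong.

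**Conclusion.** The point holds conditionally. The design stratifies by area and gender, and the described model names neither. If the ten area-by-arm groups are used as clusters without area, the interval is too wide: the standard error is 15% / 35% too large at an assumed area share of 2% / 5% with no singing-group variance. The test is then conservative, at the power and type I error shown in step 3. Under plain ANCOVA the effect is minor, about 1-5% of the standard error across area shares of 2-10%, and it is nil if the level is area. Validity is not threatened, since the randomised comparison remains unbiased. The case for change is that the analysis should reflect the randomisation, not that more power is assured.

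**What to change.** In the primary model, and in the secondary models that follow it, include area (five levels) and gender as fixed covariates beside the baseline score. Apply any singing-group random effect on top of area, and state the cluster unit for each arm, including how controls, who do not meet, are represented. State which degrees of freedom the test uses.

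Both factors are already in the randomisation record, so no new data are needed. The cost is five model degrees of freedom (four for area, one for gender). If a group random effect is tested on cluster-level degrees of freedom, the drop from 8 to 4 can reduce power when area variance is small (step 4), so the method should be chosen with that in view before unblinding.

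### The exploratory per-protocol analysis filters only the singing arm on attendance, so it is not a randomised estimate of efficacy and may be biased in either direction

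*Protocol article*

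**What the plan says.** Under Effectiveness analysis, the protocol article makes intention to treat primary: "participants are analysed as part of their randomised group irrespective of their attendance". The SF-12 is to be "analysed at 6 months using analysis of covariance to adjust for baseline differences between the groups", with multi-level modelling for clustering within singing groups.

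The same section then adds: "We will also explore the potential efficacy of the intervention", by means of a "per protocol analysis in which only those participants who attended at least 50% of sessions are included". It gives no separate rule for controls and names no method for selection related to adherence.

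Two other sections bear on the rule:

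- **Control:** "Individuals in the control group will continue with their normal activities". On singing elsewhere: "Should they decide to join a singing group outside the research they will not be excluded but data will be collected on these activities".
- **Secondary outcomes:** the process data cover "individual attendance at singing groups for participants". The Intervention section provides for an attendance register at each club.

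**The concern.** The inclusion rule depends on something that happens after randomisation and that only one arm can do. Attendance may depend on health, mobility and mood, and the SF-12 measures health in both its physical and mental aspects. Once low attenders are dropped from one arm and nobody is dropped from the other, the two sets need not be comparable, even in a trial where singing has no effect.

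What is at stake is interpretation. A per-protocol estimate placed beside a smaller intention-to-treat estimate invites the reading that singing works for those who take part. Part or all of that gap could come from who attends. The article criticises earlier singing studies for showing no evidence of randomisation, and this analysis brings a non-randomised contrast back into the trial.

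**Working it through.** **1. Inputs from the plan (Sample size section).** A 5-point difference is equated with an effect size of 0.5, so SD = 5 / 0.5 = 10. Check of the stated size per arm: 2 × (1.96 + 0.842)² / 0.5² = 62.8, so 63, as stated. The design effect is 1 + (12 − 1) × 0.02 = 1.22, and 63 × 1.22 = 76.9, so 77, as stated. I use SD 10 and 77 analysed per arm below.

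**2. Inputs not in the plan (assumptions).** p is the share of the singing arm attending at least half the sessions, taken as 0.6 to 0.8. r is the correlation between attendance propensity and the 6-month score after baseline adjustment, taken as 0.2 to 0.3. I assume no true effect, a normally distributed propensity, all controls kept, and the baseline-adjusted model of the primary analysis.

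**3. Spurious effect.** Attenders are those above the cut t = Φ⁻¹(1 − p). Their mean propensity is φ(t)/p, which is 0.350 at p = 0.8, 0.497 at p = 0.7 and 0.644 at p = 0.6. Spurious effect = r × φ(t)/p × SD.

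| p | r = 0.2 | r = 0.3 |
|---|---|---|
| 0.8 | 0.70 points | 1.05 points |
| 0.7 | 0.99 points | 1.49 points |
| 0.6 | 1.29 points | 1.93 points |

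Against the 5-point target this is 14% (0.70 / 5) to 39% (1.93 / 5).

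**4. Scaling.** Because r refers to the baseline-adjusted score, the consistent multiplier is the residual SD, 10 × √(1 − c²), where c is the correlation between baseline and 6-month score. The article does not give c. At an assumed c = 0.5 it is 8.7, which makes the effects 13% smaller; at c = 0.7 it is 7.1, which makes them 29% smaller. The range then runs from 0.70 × 0.714 = 0.5 to 1.93 × 0.866 = 1.7 points.

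**5. False positives.** With 77 controls and 77 × p attenders, and clustering ignored, SE = 10 × √(1/(77p) + 1/77). This is 1.71 at p = 0.8 and 1.86 at p = 0.6. The two-sided type I error, nominally 5%, becomes 6.9 to 10.6% at r = 0.2 and 9.4 to 18.0% at r = 0.3. If bias and SE shrink together with the residual SD, these rates do not change.

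**6. Direction.** The formula is linear in r. At r = 0 there is no bias. At r = −0.2 to −0.3 the figures in step 3 change sign, and the analysis understates any benefit.

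**The case against.** **The analysis is subordinate.** It is worded as exploration. The hypotheses, the sample size and the primary analysis do not depend on it. This stands, and it limits the weight of the point.

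**A reader might infer that the rule removes every control.** Taken word for word it would, since no control has sessions to attend. That reading is strained: an attendance rule naturally addresses those who were offered sessions, and nobody would plan a between-arm analysis with an empty arm. How controls enter the set is also a detail that an article may leave to the full plan. The point does not need that reading, because keeping all controls is what produces the one-sided selection.

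**A reader might infer that the analysis will show benefit even if singing does nothing.** The documents do not support that. They nowhere say that fitter or happier people attend more. Isolated or low-spirited volunteers may attend most, and fitter people may be busier. Baseline adjustment also removes much of the selection on baseline health. At r = 0.2 the bias is only 0.4 to 0.7 standard errors (0.70 / 1.71 and 1.29 / 1.86). What remains is that baseline adjustment cannot deal with changes in health after baseline that affect both attendance and the 6-month score.

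**CACE is not free of assumptions.** With a cut at half the sessions, it assumes that attending fewer has no effect. If partial attendance helps, the estimate is too large. It also divides the intention-to-treat effect by the share attending, so it too exceeds that effect in size. This is fair, and the assumption must be stated. The difference is that CACE is built on the randomised contrast: if assignment has no effect, its expected numerator is zero whoever attends.

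**Conclusion.** The point holds as a fault in a stated rule for a secondary analysis. Filtering one arm on attendance after randomisation does not give a randomised estimate of efficacy. The result is unbiased only if attendance is unrelated to outcome given baseline, which the article neither states nor supports.

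The possible size is modest but not negligible: about 0.7 to 1.9 points at SD 10, or about 0.5 to 1.7 on the residual SD. These figures rest on assumed values for attendance, for the attendance–outcome correlation and for the baseline–outcome correlation; none is in the article. The sign is also assumed and could reverse. The documents do not support saying that the analysis has no comparator or that it is bound to favour singing. The intention-to-treat result is untouched, so this is worth correcting but does not threaten the trial's main conclusion.

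**What to change.** Make the efficacy analysis a CACE analysis:

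- Use randomised arm as the instrument and attendance at half or more of the sessions, from the register, as the exposure.
- Keep all randomised participants in both arms, with the same covariates and clustering adjustment as the primary model.
- State the exclusion restriction: assignment to singing has no effect on those who attend fewer than half the sessions.
- Add one sensitivity version with number of sessions attended as the exposure, and one that counts controls' recorded outside singing as exposure.

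If the per-protocol analysis is kept, state that all controls are retained and label the result a non-randomised comparison.

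**Cost.** No new data are needed, because attendance and outside singing are already to be recorded. The interval widens by roughly 1/(share attending): 1/0.8 = 1.25 times at 80% and 1/0.6 = 1.67 times at 60%. The estimate also relies on the exclusion restriction, which the sessions-attended version probes but cannot prove.
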